## Abstract

**Introduction:**

Scotland is the first country to carry out a national implementation of minimum unit pricing (MUP) for alcohol. MUP aims to reduce alcohol-related harms, which are high in Scotland compared with Western Europe, and to improve health equalities. MUP is a minimum retail price per unit of alcohol. That approach targets high-risk alcohol users. This work is key to a wider evaluation that will determine whether MUP continues. There are three study components.

**Methods and analysis:**

Component 1 sampled an estimated 2800 interviewees at a baseline and each of two follow-ups from four Emergency Departments in Scotland and Northern England. Research nurses administered a standardised survey to assess alcohol consumption and the proportion of attendances that were alcohol-related.

Component 2 covered six Sexual Health Clinics with similar timings and country allocation. A self-completion survey gathered information on potential unintended effects of MUP on alcohol source and drug use.

Using a natural experiment design and repeated cross-sectional audit, difference between Scotland (intervention) and North England (control) will be tested for outcomes using regression adjusting for differences at baseline. Differential impacts by age, gender and socioeconomic position will be investigated.

Component 3 used focus groups with young people and heavy drinkers and interviews with stakeholders before and after MUP implementation. The focus groups will allow exploration of attitudes, experiences and behaviours and the potential mechanisms by which impacts arise. The interviews will help characterise the implementation process.

**Ethics and dissemination:**

Study components 1 and 2 have been ethically approved by the NHS, and component 3 by the University of Stirling. Dissemination plans include peer-reviewed journal articles, presentations, policy maker briefings and, in view of high public interest and the high political profile of this flagship policy, communication with the public via media engagement and plain language summaries.

**Trial registration number:**

ISRCTN16039407; Pre-results.

Strengths and limitations of this studyThis evaluation adopts multiple methods to help establish whether minimum unit pricing (MUP) has caused changes in alcohol-related attendances using a natural experiment design, which is the most appropriate for this topic as a randomised controlled trial would not be feasible.Our study exploits divergences in Scottish and English alcohol policy to evaluate the effectiveness of an all-beverage MUP for the first time, and evaluates both positive and possible negative impacts of MUP of alcohol; such negative impacts might include use of other sources of alcohol, other substances or reduction in money available for essentials.The Northern English control group is likely to be comparable to Scotland because of geographical proximity and similar levels of deprivation, but we also assess the external validity of our sample by reference to routine data on attendances at Emergency Departments and Sexual Health Clinics.There is the potential to follow-up individuals through longer term data linkage, for which we will obtain respondents’ permission, thus adding a cohort dimension to the initial cross-sectional approach.The main limitation is that the non-randomised design risks selection bias, for example in the differential selection of intoxicated attendees for interview.

## Introduction

Minimum unit pricing (MUP) of alcohol is a novel public health policy that aims to reduce alcohol-related harms across the population. In May 2012, Scotland became the first country to pass legislation to introduce MUP without reference to beverage type, a politically high profile measure,^1–3^ although some Canadian provinces have introduced beverage-specific MUP, as further described below. This paper describes the protocol for three associated studies that collect primary data to evaluate the impact of the policy in Scotland. After delays following legal challenges,^4 5^ MUP legislation was implemented in May 2018 but it is due to cease in 6 years unless shown to be effective, under a ‘sunset clause’. These studies are a key part of the evaluation planned by NHS Health Scotland, which will report to Scottish Ministers and the Scottish Parliament. The evaluation includes analyses by others of routinely collected administrative data.^6^

The overall aim of the study is to investigate the impacts of MUP on acute and chronic health harms (including by deprivation and gender and age subgroups). The study will also determine the extent to which specific unintended consequences occur. The evidence will be a key input to the decision whether the policy will continue.

Alcohol consumption is a major determinant of population health globally,^7^ and the level of alcohol-related harm in Scotland is high compared with the rest of Western Europe.^8^ Alcohol is associated with over 200 medical conditions including an increased risk of liver disease, heart disease, unintended pregnancy, sexually transmitted infections, some cancers and some injuries.^9–14^ Its impact extends beyond the individual, with adverse effects on families, communities and the wider economy.^15 16^ Furthermore, alcohol is known to be a major contributor to socioeconomic inequalities in health in the UK and elsewhere.^17–20^ From a public health perspective, alcohol therefore has considerable potential as a modifiable risk factor to be addressed to help reduce health inequalities.^21–23^

A consistent body of international evidence demonstrates a negative relationship between price, consumption and alcohol-related harms.^24–28^ The WHO has identified changing the price of alcohol, and controls on promotion and availability, as key methods for addressing alcohol-related health harms.^29–31^ Across much of the world, the best established mechanism for influencing price has been taxation through alcohol duty, although in many countries, including the UK, the primary purpose is revenue-raising for central government rather than achieving public health goals.^32^ As a result of this secondary consideration of public health, alcohol duty may be poorly designed to address alcohol-related harms since duty typically varies by product in a manner not consistent with the associated harms arising from the product’s consumption. At the time of writing tax on a litre of 7.5% alcohol by volume (ABV) cider is 40 pence, on a litre of wine of the same strength tax would be 289 pence.^33^

A potentially complementary approach to increasing alcohol duty is the introduction of a floor price, such as MUP, below which alcohol should not be retailed.^34 35^ MUP sets a minimum price per UK unit (8 gm) of pure alcohol. Epidemiological studies have found that drinkers at the greatest risk of harm tend to consume the cheapest (per unit) alcohol, thereby providing evidence that MUP may better target harmful drinkers in comparison to alcohol duty.^36 37^ Econometric modelling studies suggest that MUP will result in a greater reduction in health harms compared with an equivalent rise in taxation under the UK’s current system of calculating alcohol duty.^21 22 38–40^ In addition, setting a floor price minimises the potential for ‘trading down’ to cheaper drinks, given that alcoholic drinks below the floor price would no longer be legally available. This is particularly relevant since previously retailers have opted not to pass on alcohol duty increases to consumers, as indicated by the existence of below-cost products.^41^

Comparable interventions to MUP have been introduced elsewhere. The best known example is in Canada, where some Canadian provinces introduced a minimum price for selling specific beverages (also referred to as ‘reference pricing’) within the context of government-operated monopolies.^42 43^ While some authors refer to these interventions as ‘minimum pricing’, the nature of this policy differs in some aspects from ‘MUP’ as planned in Scotland.^3 5 44^ In contrast to MUP which applies a uniform minimum price per unit across all beverage types, reference pricing imposes differing minimum prices that are determined by both alcohol strength and drink type. In addition, MUP in Scotland was introduced into a competitive alcohol market at a national level, in contrast to the locally applied government-owned monopolies in which reference pricing has been introduced. Important benefits of reference pricing in Canada have been demonstrated, with reductions in alcohol consumption, alcohol-attributable hospital admissions and crime observed.^45–50^ However, a study focusing on Emergency Department (ED) visits found no reduction in overall visits for alcohol-related injuries, although alcohol-related motor vehicle injuries did fall.^51^ Other broadly comparable pricing interventions, such as the abolition of cheap vodka within communist Russia, have similarly been associated with reductions in alcohol-related mortality.^52^

In Scotland, qualitative research has investigated the policy process through which MUP developed, including assessing the role of commercial interests, and seeking to identify transferable lessons for public health advocacy.^3 5 44 53–57^ The influence of econometric modelling has been specifically investigated.^58 59^The dominant media discourses and the roles of different policy stakeholders in articulating arguments to the public have been explored using content analysis of newspaper reporting and trends in newspaper coverage have been tracked over time.^60–63^ The views of the public and heavy drinkers around MUP have also been investigated.^64–67^ There remained a need to investigate the views of policy stakeholders, the public and heavy drinkers about MUP as implemented.

Empirical research gathering primary data specifically focused on MUP in Scotland remains limited. The introduction of MUP provides a unique opportunity to use a natural experiment to evaluate public health policy, and provide new real-world evidence on the effectiveness of MUP, where most evidence to date has been from modelling studies.^68 69^ A broad programme of research is being co-ordinated by NHS Health Scotland, which will report to Scottish Ministers and the Scottish Parliament between five and 6 years after the start of the policy. This programme includes analyses of administrative data and alcohol sales data.^70^ The protocol described here complements the NHS-led work and has been funded by the National Institute for Health Research Public Health Research programme to collect primary data in three associated studies.

Much of the burden of alcohol-related harm, especially among young people, arises from acute harm following high episodic consumption (‘binge drinking’). These harms are of particular interest to policymakers as they may be associated with social disorder and violence. That in turn provides one justification for MUP, although the case for MUP legislation in Scotland was fought (and won) on public health benefits. Comprehensive diagnostic data on ED alcohol-related attendances that do not result in admission are currently not adequately captured in administrative health data within the UK, so require primary research.

Our work focuses on both intended and possible unintended consequences of the intervention.^71^ A number of potential risks arising from the introduction of MUP have been identified by policymakers, the alcohol industry and public health professionals.^54^
Consumers may switch to alternative sources of alcohol not subject to MUP so that the price paid does not increase. Such sources include both legal sources: internet sales from outside Scotland, legitimate cross-border purchase for own use and home fermentation and illegal sources (counterfeit and unlicensed sale of smuggled or stolen alcohol).Increased alcohol-related harm could occur through substitution (eg, to illicitly produced or industrial alcohol associated with greater toxicity) or changed drinking patterns (eg, moving from regular drinking to binge drinking).Displacement effects with reductions in alcohol-related harms potentially accompanied by increases in harms related to other substance use.MUP could unfairly penalise deprived populations less able to absorb the additional financial cost and this may adversely affect access to essentials such as food and fuel.MUP may have unintended effects on harmful drinkers who cannot reduce their consumption.There may be adverse economic impacts on the Scottish alcohol industry retailers and/or manufacturers.

The ED and Sexual Health Clinics (SHC) studies described in this protocol will address the first four of these potential risks, although analysis of existing datasets by NHS Health Scotland will further address the potential impact on access to essential goods. A study has been commissioned from the University of Sheffield by NHS Health Scotland to assess the effects on harmful drinkers. The possible adverse economic impact on the Scottish alcohol industry will not be addressed by our project but will be monitored by the Scottish Government through the Monitoring and Evaluating Scotland’s Alcohol Strategy (MESAS) studies managed by NHS Health Scotland.

It was not possible to collect sufficiently valid consumption data in the ED setting to assess alcohol consumption levels based on consumption owing to interview time constraints. Instead, we defined hazardous, harmful and dependent alcohol consumption using scores from the Fast Alcohol Screening Test (FAST).^72^ The use of FAST to identify alcohol misuse (ie, hazardous, harmful and dependent alcohol consumption) has been supported by national guidelines for the prevention of harmful drinking.^73^ Derived from the AUDIT^74^ the four item FAST was specifically developed and validated within ED as it is quick to administer and less disruptive in the busy ED setting.^72 75^ The FAST has been found to be the most sensitive and accurate short alcohol screening tool commonly administered to identify alcohol misuse in adults attending ED.^76 77^ and has been used in a number of clinical studies.^78 79^ A score of ≥3 on the FAST indicates hazardous drinking. We are undertaking a parallel examination of The FAST screening tool to further discriminate alcohol use disorders in ED attendees. In our study MUP is theorised to reduce alcohol misuse (hazardous, harmful and dependent alcohol consumption), so reducing both acute and chronic alcohol-related harm, and therefore the numbers of alcohol-related attendances at both EDs and at SHCs. Hazardous drinkers are expected to be more likely than harmful or dependent drinkers to present with acute harms (such as injuries and assaults), while harmful/dependent drinkers are likely to present with both acute conditions and acute consequences of chronic conditions (such as pancreatitis and gastritis). Therefore there may be an early impact on ED attendances relating to chronic as well as acute alcohol-related conditions.

## Research questions

The more specific research questions and objectives are summarised in table 1, with the contribution of each of the three study components stated.

**Table 1 T1:** Research aims and study components

Research aims (RAs)	Study components (C)
RA1: To determine the impact of MUP on alcohol-related harms and drinking patterns for the overall population and by subgroups of interest (age, sex and socioeconomic position).	ED study of alcohol-related attendances (C1); Survey of alcohol-related behaviours (consumption patterns, alcohol spend, source of alcohol, move to other substances) in SHCs (C2)
RA2: To determine the impact of MUP on non-alcohol substance use, and other unintended impacts, for the overall population and by subgroups of interest (age, sex and socioeconomic position).	Survey of alcohol-related behaviours in SHCs (C2); Qualitative focus group study and stakeholders (C3)
RA3: To describe changes in experiences and norms towards MUP and alcohol use following the introduction of MUP by subgroups of interest (age, sex and socioeconomic position).	Qualitative focus groups with young people/heavy drinkers and interviews with stakeholders from public services (C3)

ED, Emergency Department; MUP, minimum unit pricing; SHC, Sexual Health Clinics.

Another separately funded study is focusing on the impacts on people with alcohol dependence, including high rates of homelessness specifically. We therefore do not target this group for our qualitative work.

At the time of revising this paper for referees’ comments, all data have been collected for all three components and analysis will shortly commence.

## Methods and analysis

### Component 1: audit of alcohol-related attendances at EDs

#### Study design

This component is designed to quantify changes in alcohol-related attendances at ED settings as a result of MUP. The FAST is used to identify alcohol misuse in the ED. The component focuses on answering research aim (RA)1, namely:What are the impacts of MUP for alcohol on alcohol-related harms and drinking patterns (using the FAST) for ED attendees and by subgroups of interest (age, sex and deprivation)?Does the effect of MUP vary dependent on the type of alcohol-related harm:Acute alcohol-related harms vs chronic alcohol-related harms?Broad diagnostic groups (based on coding systems used in EDs?
Does MUP affect alcohol consumption (on the basis of the FAST^72^ score and alcohol misuse over the reporting period among people attending EDs (FAST >3)?Does the MUP intervention effect size (assessed on a variety of measures including FAST) vary at the second and third time points?

Lower level outcomes are set out in the Data collection section. To answer RA1, a natural experiment design employing a repeated cross-sectional audit of all alcohol-related attendances at EDs in two Scottish hospitals and two North of England comparator hospitals at three time points was most appropriate to assess causality. A Randomised Controlled Trial was not feasible. The study methods and tools were based on previous studies used to quantify the national prevalence of alcohol-related attendances in EDs in England^79^ and informed by the experience of the Scottish ED Alcohol Audit, carried out across 15–20 hospitals throughout mainland Scotland between October 2005 and June 2007.^80^

#### Study population

People aged 16 years and over attending EDs during data collection periods were approached. The study monitored, but excluded from interview:those acutely physically or mentally ill such that informed consent or full participation was impossible to obtain (including gross intoxication),those with whom it was impossible to adequately communicate (eg, patients unable to speak English despite the use of an interpreter where available), andthose who left the department before an approach was made or who were deemed by the research nurses as too threatening to approach.

Reasons for not approaching were recorded to address potential selection bias.

#### Data collection

Baseline data collection took place in February 2018 prior to the implementation of MUP on 1 st May 2018. The second and third waves of data collection took place approximately 8 and 12 months post baseline and 5 and 9 months post implementation, with care taken to avoid the inclusion of specific events that are expected to be associated with increased or decreased alcohol consumption, for example local holidays were checked to avoid differences between groups. Each wave collected data over 3 weeks, and to maximise collection of both alcohol-related attendances and alcohol misuse, data collection occurred from 20:00 to 03:30 from Thursday to Sunday (ie, 30 hours per week during this time period) and 09:00 to 16:30 from Monday to Wednesday (ie, 22.5 hours per week during this time period).

During study data collection periods, patients were approached by a research nurse to seek permission to complete a short face-to-face interview. All eligible patients were approached, informed consent obtained and a face-to-face interview based on a previously used patient questionnaire was administered electronically using a tablet (iPad).^78^ An ED attendance database was maintained for all attendances during data collection periods to allow monitoring of patient recruitment.

The interview collected details on the following:basic demographic information (age; gender; ethnicity; marital, employment and housing status (including unstable housing status such as no fixed abode and hostel accommodation); postcode sector);attendance details (date and time, triage category, time and date of incident);how much alcohol was consumed in the past 24 hours;date, time and place of last drink;the largest number of drinks on any 1 day in the previous week;self-reported reason for attendance, such as assault, collapse etc;alcohol misuse in the past year (as assessed by the FAST)^72^ andwhether alcohol consumption changed over the previous 12 months.

In addition we asked whether interviewees thought their current ED attendance was related to their or someone else’s drinking, and how many times they had attended any ED in the previous 12 months.

A note was made of the hospital unique identifier for the attendance if participants agreed to link their research interview data to their ED data. Research staff retrieved additional data from patient records on full postcode, triage category, discharge status and diagnoses at discharge (coded by International Classification of Diseases (ICD)-10 or other ED coding systems in use locally). The consent procedure asked participants for separate permissions both for this and for data linkage to facilitate longitudinal follow-up. Additionally, aggregated data on age group, sex and diagnosis were sought for all attendees in the study time periods in order to allow an assessment of the representativeness of the interviewee sample.

#### Socioeconomic position and inequalities

Analysis by deprivation, age and sex will be undertaken to determine if the impact of MUP on alcohol-related attendances at EDs is differentially patterned. Assessment of alcohol-related attendances within the ED setting provides a broad range of deprivation, age, sex and drinking status categories. It therefore not only provides information on an important primary health outcome but also allows adequate investigation of the intervention’s impact on important subgroups.

#### Outcome measures

The primary outcome will be the proportion of attendances that are alcohol-related, using a composite measure which defined the attendance as alcohol-related if any one (or more) of the following was true:patient self-reports attendance is alcohol-related;patient reports alcohol consumption in past 24 hours >8 units in men, >6 units in women; orpatient not approached or interview terminated because too intoxicated with alcohol.

Secondary outcomes will be:the absolute number and proportion of alcohol-related attendances;alcohol misuse defined by the FAST score >3;mean FAST score by age, gender and deprivation;prevalence of binge drinking in the past week, andself-reported reason for attendance.

Outcomes will be compared between intervention and control areas, adjusted for baseline attendances.

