#### Power calculation

Based on the experience of the 24 hours audit of EDs in England,^79^ and assuming that we would be able to recruit 50% of eligible ED attendees, we anticipated that the four sites (two Scotland, two England) would result in 940 recruits per week. Recruiting over 3 weeks pre-implementation and post-implementation—giving a total sample size of 5640 for the baseline and any one subsequent wave—would mean that we would be highly powered (>80%) to detect an effect size of ±5% in the proportion of alcohol-related attendances from an estimated 30% with 95% significance. We have used a base rate of 30% informed by the 24 hours audit of EDs in England^79^ and assumed a 5% decrease would be of public health importance and may be expected based on current evidence.^79^ For subgroup analyses, we would have good power (>80%) to detect an effect size of 0.23 on the FAST score among those from the most deprived quintile (estimated to be 25% of attendances) and an effect size of 0.27 among those aged 18–24 years (estimated to be 15% of attendances).

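### The Component 1 primary composite mixes cases counted across all attendances with cases found only among recruits, so unweighted the proportion and the absolute number both move with the recruitment rate

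*Protocol article*

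**What the plan says.** All references are to Component 1 of the protocol article unless noted.

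- **Outcome measures.** "The primary outcome will be the proportion of attendances that are alcohol-related, using a composite measure". Any one of three criteria suffices: "patient self-reports attendance is alcohol-related"; "patient reports alcohol consumption in past 24 hours >8 units in men, >6 units in women"; or patient "not approached or interview terminated because too intoxicated with alcohol". The secondary outcomes include "the absolute number and proportion of alcohol-related attendances". The denominator is given only as attendances. The one adjustment named here is for baseline attendances.
- **Study population.** Grossly intoxicated patients belong to the groups that "The study monitored, but excluded from interview". Reasons for not approaching were recorded in order to address possible selection bias.
- **Data collection.** "An ED attendance database was maintained for all attendances during data collection periods to allow monitoring of patient recruitment". Aggregate age, sex and diagnosis data were also sought for all attendees, to judge how representative the interviewees are.
- **Power calculation.** The sample size rests on "assuming that we would be able to recruit 50% of eligible ED attendees", a base rate of 30% and a change of 5 points.
- **Statistical analysis.** The model has ED as a fixed effect and adjusts for baseline level of alcohol-related attendance, age, gender, deprivation quintile and diagnostic category. Recruitment does not appear.

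**The concern.** The composite joins two sampling fractions. A patient not approached because too intoxicated needs no consent and can be counted from the attendance monitoring, so this group enters at close to its full number. A patient who meets either interview criterion is detected only if recruited, which is planned to happen about half the time. Added together without weights, the two parts give neither a proportion of attendances nor a proportion of interviewees. Each too-intoxicated attendance carries about twice the weight (1/0.5) of any other attendance.

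Two things follow. The level of the primary outcome depends on how many eligible patients the nurses manage to interview. And if recruitment changes between waves in one country but not the other, the Scotland-England contrast shifts with no change in drinking. A raw count of detected cases is more exposed still, because its interview-detected part is proportional to recruitment. This is the primary outcome of a study that the Introduction describes as a key input to the decision on whether the policy continues.

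**Working it through.** **The plan's own figure.** 940 recruits per week x 3 weeks x 2 waves = 5,640, as stated. That is 2,820 per wave, or 1,410 per country per wave if split equally. A two-group comparison of 1,410 v 1,410, two-sided 5%, has power 84.5% for 30% v 25% and 80.9% for 30% v 35%. So the stated power above 80% reproduces as a simple two-group contrast. The plan thus takes 30% as its base rate and sizes the study on recruits.

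**Inputs.**
- True proportion alcohol-related: 30% (Power calculation).
- Recruitment among eligible attendees, *r*: 50% planned (Power calculation); 40% and 60% are illustrative.
- Share of attendances too intoxicated, *g*: not in the article; assumed 1%, 3% and 5%.
- Attendances here means eligible plus too intoxicated. Interviewees are assumed to represent eligible attendees.

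**Formulas.** Alcohol-related attendances among the rest make up 0.30 - *g* of the total.
- Unweighted proportion, interviewees plus too-intoxicated: A = [*g* + *r*(0.30 - *g*)] / [*g* + *r*(1 - *g*)].
- Detected cases per attendance (raw count): C = *g* + *r*(0.30 - *g*).

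**Example at *g* = 3%.**
- *r* = 50%: A = 0.165/0.515 = 32.0%.
- *r* = 40%: A = 0.138/0.418 = 33.0%.
- *r* = 60%: A = 0.192/0.612 = 31.4%.
- Count from 50% to 40%: 0.138/0.165 - 1 = -16%.

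**Recruitment falls from 50% to 40%, true proportion unchanged at 30%.**

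| *g* | A at 50% | A at 40% | Shift in A | C at 50% | C at 40% | Change in count |
|---|---|---|---|---|---|---|
| 1% | 30.7% | 31.0% | +0.3 points | 0.155 | 0.126 | -19% |
| 3% | 32.0% | 33.0% | +1.0 points | 0.165 | 0.138 | -16% |
| 5% | 33.3% | 34.9% | +1.6 points | 0.175 | 0.150 | -14% |

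For scale, the target of 5 points from 30% is 5/30 = 17% relative.

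**Constant recruitment of 50%.** The double weight still acts if the too-intoxicated share changes. Suppose *g* falls from 3% to 2% because patients equal to 1% of attendances become interviewable but are still alcohol-related. The true proportion stays at 30%, yet A falls from 32.0% to 0.160/0.510 = 31.4%. A shift in the nurses' threshold for calling a patient too intoxicated would do this.

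**Check of the remedy.** Weighting interviewees by 1/*r* gives [*g* + (0.30 - *g*)] / [*g* + (1 - *g*)] = 30.0%. The recruitment rate cancels whatever its value.

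**The case against.** The strongest reply is that the faulty estimator is inferred. The article does not say that the analysis is unweighted or that the absolute number is a raw count, and an analysis plan that is not shown could weight or scale by recruitment. The authors recognise the risk: they list differential selection of intoxicated attendees as the main limitation, recorded reasons for not approaching to address selection bias, and hold the data needed for a correction. This stands as to intent. But the article does fix the composite and does name its adjustments, and none of them corrects for recruitment.

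The second reply is that much of the effect cancels. Stable differences between EDs are largely absorbed by the ED fixed effect and baseline adjustment, and changes common to both countries largely drop out. Both countries used the same collection windows and the same rule of approaching every eligible patient. This stands, and it limits the bias in the policy contrast to differential change by country and wave.

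A reader might infer more than the documents support:
- *That the false change in the count exceeds any plausible policy effect.* At -14% to -19% it is about the same size as the plan's own 17% relative target, and the count is a secondary outcome.
- *That the artefact reaches half of the 5-point target.* That needs 5% too intoxicated and a 20-point recruitment gap, 40% v 60%, arising in one country only (34.9% v 32.3%, or 2.6 points).
- *That non-interviewed patients are scored as negative.* At 3% too intoxicated and 50% recruitment this would give 16.5%, which does not fit a plan built on 30%, and nothing in the article says it.
- *That every intoxicated patient is captured.* Terminated interviews occur only after an approach, and some intoxicated patients may be logged as having left or as too threatening.

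**Conclusion.** The concern holds as a fault in how the primary outcome is specified. As written, the composite combines two sampling fractions with no stated denominator and no stated correction, so an unweighted proportion and a raw count both vary with recruitment. The shift in the proportion is modest: about 1 point or less per 10-point change in recruitment if 1% to 3% of attendances are too intoxicated, and 1.6 points at 5%.

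The sizes rest on an assumed too-intoxicated share, on near-complete capture of that group, and on 50% as a planning figure; realised recruitment is not reported. The documents do not show that recruitment, or the threshold for too intoxicated, in fact moved differently in the two countries. So they do not support saying that the policy estimate is biased, only that the outcome as defined leaves it open to such bias.

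**What to change.** The Research questions section says that data are collected and analysis is about to start, so the change can be made beforehand.

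1. State the denominator: attendances aged 16 and over in the collection windows that are either eligible for interview or too intoxicated.
2. Count each too-intoxicated attendance once. Weight each interviewee by eligible attendances divided by interviewed, within ED x wave x collection window, from the attendance database.
3. Use the weighted proportion as the primary outcome. Derive the absolute number as that proportion times the attendances in the same denominator.
4. Report recruitment and too-intoxicated counts by ED and wave.
5. As sensitivity analyses, give the unweighted result and a version that extends the weights to all other non-interviewed attendances. The main weights should not silently let interviewees stand in for patients excluded as acutely ill, unable to communicate, threatening or already gone.

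The cost is some analysis wording and a weight variable from data already held. The price is slightly wider intervals and an assumption that interviewees represent eligible non-interviewed patients within each cell.
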